**Process evaluation**

**Economic evaluation**

A rigorous and systematic approach to the economic analysis will be applied applying international standard best practice methods for the design and conduct of economic evaluations in health care (Drummond et al., 2015; Brazier et al., 2016). The cost-effectiveness of the proposed intervention will be estimated using a cost-utility analysis (CUA) undertaken alongside the RCT with quality adjusted life years gained (QALYs) as measured by the EQ-5D-5L as the main measure of outcome. The purpose of the economic evaluation is to compare the differences in the streams of outcomes and resource use that will occur as a consequence of the introduction of the mobile phone app. This will be expressed in terms of the incremental cost per QALY gained in the Australian setting. A health system perspective will be taken for the economic evaluation including health related resource use (costs and cost-offsets) and health related quality of life outcomes. As the economic evaluation will be conducted alongside the clinical trial with a 9 month follow up period, discounting of costs and benefits beyond the base year of the economic evaluation will not be necessary. The setting of the economic evaluation will be the Australian health care setting.

The intervention will be tested in the RCT in the circumstances in which it will be expected to be applied should it be adopted for wide-spread routine application within the health system. The main clinical outcomes of the RCT encapsulate directly measured and reported participant relevant end points. The follow up period of 9 months is an appropriate time horizon within which all patient relevant end points will be adequately captured.

**Data analysis**

The primary analyses will be based on a between-group (intervention arm vs control arm), intention-to-treat approach at the different time points. Continuous variables will be analysed using independent t-tests and discreet variables will be analyses using chi-squared tests. Where appropriate, other statistical tests will be employed depending on the nature of the data. Identification of any confounding baseline variables will be corrected by logistic regression analysis. All between group outcome results that are significant will be reported with odds ratios and 95 % confidence intervals. Statistical significance is set at α 0.05.

Qualitative outcomes

Thematic analysis will be carried out based on patient responses to open-ended questions in the functional assessments. This will enable to generate emerging and overarching themes. The analysis will characterise intervention arm participants’ observed and self-reported responses to the intervention and link these responses to the acceptability, utility and their engagement with the smartphone app. This thematic analysis will be based on the intervention arm participants’ responses collected at months 3 and 9, in addition to a satisfaction survey undertaken upon completion of the trial.

Economic outcomes

Data on the frequency and duration of hospital in-patient admissions will be obtained from medical records, and PBS and MBS utilisation data from Medicare following informed patient (or proxy in the case of moderate to severe cognitive impairment) consent. Unit costs will be derived from relevant hospital finance departments, published data sets including Pharmaceutical Benefits Scheme and Medicare Benefits Schedule and Australian Refined Diagnosis Related Groups (AR-DRG) cost weights.

A participant level analysis will be undertaken to determine the incremental costs and outcomes associated with the intervention relative to controls. Incremental cost effectiveness ratios and their associated confidence intervals will be estimated and cost effectiveness acceptability curves for varying threshold values of cost effectiveness will also be presented. An assessment of the sensitivity of the results obtained to variation in measured resource use, effectiveness and/or unit costs will be undertaken using appropriate one-way, multi-way and probabilistic sensitivity analysis.

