**Hypothesis**:

The primary hypothesis is that reminders via a smartphone application with a personalized and progressive monitoring system plus usual care (as received by participants in the intervention arm) compared with usual care alone (as received by participants in the control arm) will be associated with higher medication adherence, at 9 months’ follow up.

The secondary aims of this trial includes:

1. to determine whether a smartphone application reminder with interactive and personalised monitoring is cost effective, as determined by lower health services utilization, at 9 months’ follow up;

2. to determine the impact of the smartphone application on signs and symptoms of heart failure and quality of life at 6 and 9 months;

3. to determine whether the intervention is associated with higher medication and heart failure knowledge;

4. to determine the feasibility, acceptability and engagement with the application as determined by the

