**Outcome measures**

Outcome measures will be collected at 3, 6 and 9 months following the baseline data collection at recruitment.

Primary outcome

The primary outcome is the comparison of medication adherence between the two arms. Medication adherence will be measured by self-reported medication adherence tool Self-Efficacy for Appropriate Medication Use Scale (SEAMS) (Risser et al., 2007). This has been validated previously in other cardiac conditions such as coronary heart disease (Risser et al., 2007). This self-reported data will also be verified by the data collected from the intervention arm participants whose adherence rate has been captured by the data collected by the NPS MedicineWise application.

Secondary outcomes

i. composite outcome of death or hospital admission related to HF or not related to HF. All instances of hospitalization and death will be recorded and classification as to whether it was HF related or not will be done by experienced cardiologists

ii. health resource utilization (ie. Primary and secondary care contacts, social care contacts and relevant medication use)

iii. health related quality of life, assessed by EQ-5D-5L

iv. self-reported medication adherence

v. assessment of exercise tolerance (6 min walk test)

vi. psychological wellbeing (Depression anxiety and stress scales)

vii. self-care of HF index questionnaire

viii. medication knowledge

ix. acceptability, utility and engagement with the NPS MedicineWise application (Satisfaction survey)

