**Sample size**

Sample size calculations are focused on two different measures and were also done assuming equal numbers of participants in each group. The first measure takes into account an absolute increase in mean adherence of 15 % (Hulley et al., 2013). In this measure, at two tailed 0.05 significance level with a power of 80 % and standard deviation of 35 (Goldstein et al 2014), the number of participants required in each group is 86. In the second measure, the analysis is by comparing proportions of adherence (Hulley et al., 2013). Previous studies have estimated the adherence to cardiovascular drugs to be up to 60 % (Chowdhury et al., 2013; Bowry et al., 2010). In this measure, a total sample size of 182 participants is needed to provide 80 % power to detect an increase in the proportion of adherent participants from 60 % to 80 %, with a two tailed 0.05 significance level. Therefore, taking the larger of the two sample sizes (91 participants in each arm), and allowing for a 20 % loss to follow up, a total of 220 participants will be recruited in this study with each arm consisting of 110 participants.

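### The primary hypothesis is set at 9 months, but the primary analyses are placed at several visits at an unadjusted 0.05, with no statement of which test decides

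*Protocol*

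**What the plan says.** Four sections of the protocol bear on the point.

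- **Hypothesis.** The app plus usual care, compared with usual care alone, "will be associated with higher medication adherence, at 9 months’ follow up". One time point is named.
- **Outcome measures.** "The primary outcome is the comparison of medication adherence between the two arms". It is measured with one self-report instrument (SEAMS). No time point is attached, and the text does not say whether a mean score or a proportion above a cut-off is compared. The section opens with "Outcome measures will be collected at 3, 6 and 9 months following the baseline data collection at recruitment".
- **Data analysis.** "The primary analyses will be based on a between-group (intervention arm vs control arm), intention-to-treat approach at the different time points". Tests are assigned by type of variable: t-tests for continuous variables and chi-squared tests for discrete ones. Then: "Statistical significance is set at α 0.05". There is no hierarchy of visits and no adjustment.
- **Sample size.** "Sample size calculations are focused on two different measures". The first is a difference in mean adherence. Of the other it says "In the second measure, the analysis is by comparing proportions of adherence". The larger of the two resulting sizes is used.

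**The concern.** The section that states the question and the section that governs the analysis do not agree on how many primary comparisons there are. The first gives one, at 9 months. The second uses the plural and spreads the analyses over the visits. Nothing says which section takes precedence, and nothing labels months 3 and 6 as secondary.

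Taken at its word, the Data analysis section would let a difference seen only at month 3 be presented as a positive primary analysis. That matters for a reminder app, whose effect may fade with time: an early difference that is gone by month 9 is a different finding from the one hypothesised. The same section ties the reporting of odds ratios and confidence intervals to results that are significant, which adds to the pull towards whichever visit succeeds.

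A second, smaller gap is that the form of the primary comparison (mean or proportion) is not settled anywhere.

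**Working it through.** **Inputs from the protocol.** Three post-baseline visits (Outcome measures); alpha 0.05 with no adjustment (Data analysis); mean difference 15 and SD 35, or 60% against 80%, each at two-sided 0.05 and 80% power (Sample size); 220 recruited with 20% loss (Sample size).

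**Assumed.** The correlation between the test statistics at different visits. The documents give no value, so the range 0 to 0.9 is shown.

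**1. The plan's own sizes reproduce, each for one test.**

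- Means: n per arm = 2 × [35 × (1.960 + 0.842) / 15]² = 85.5, so 86. This agrees with the plan.
- Proportions: n per arm = [1.960 × √(2 × 0.7 × 0.3) + 0.842 × √(0.6 × 0.4 + 0.8 × 0.2)]² / 0.2² = 81.2, so 82. With the continuity correction this becomes 90.9, so 91 per arm and 182 in total. This also agrees.

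Both use the full 0.05 for one comparison.

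**2. False-positive chance if any of the three visits may count.** With independent tests it is 1 − 0.95³ = 14.3%. With equal correlation ρ between visits it is 1 − P(|Z₁|, |Z₂|, |Z₃| all below 1.96), found by numerical integration:

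| Assumed ρ | Chance of at least one p < 0.05 |
|---|---|
| 0 | 14.3% |
| 0.3 | 13.6% |
| 0.5 | 12.5% |
| 0.7 | 10.9% |
| 0.8 | 9.8% |
| 0.9 | 8.4% |

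A simulation of t-tests with 91 per arm (20,000 trials per setting) gave 13.5% at ρ = 0.3 and 8.6% at ρ = 0.9, in line with the table.

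**3. If only the 9-month test counts, in one form:** 5%.

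**4. What three primary tests would need.** Bonferroni gives 0.05 / 3 = 0.0167 per test, with critical value 2.394.

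- Means: 2 × [35 × (2.394 + 0.842) / 15]² = 114.0, so 114 per arm before loss, against 86.
- Proportions without continuity correction: 109 per arm, against 82 on the same basis.
- With 91 per arm, power for 60% against 80% falls from 84% to 71%.

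The planned size therefore fits one primary test and not three.

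**5. The form of the outcome, as a hypothetical.** If adherence were tested at 9 months both as a mean and as a proportion, and either could count, simulation gives about 7.4% to 8.4%. If both forms were tested at all three visits, it gives about 15% to 21% for ρ from 0.9 down to 0.3. The cut-off for being adherent is a further assumption here, because the protocol sets none.

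**The case against.** The strongest reply is that the Hypothesis section already prespecifies 9 months, so a month-3 result would not support the stated hypothesis and the error on that hypothesis is 5%. This is right as far as it goes. The figures in step 2 are conditional on success at any visit being claimable, and no section says that it is.

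The Data analysis wording also has a harmless reading. It is the only general quantitative paragraph, so primary analyses may mean the main between-group comparisons of all outcomes, as opposed to the qualitative and economic analyses that follow. The several time points may refer to the different times set for different aims (9 months for adherence and cost, 6 and 9 months for symptoms and quality of life). This reading is possible, but the text does not fix it, and the Outcome measures section does not help because it gives the primary outcome no time point.

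A reader might also infer that there are six primary tests, three visits in two forms, with an error near 20%. The documents do not support that. Sizing on two measures and taking the larger does not commit the trial to testing both. The t-test and chi-squared sentence assigns tests by variable type and is needed anyway, because the outcomes include both binary and continuous ones. The two-form figures are upper bounds for a plan that no section states.

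Finally, detailed multiplicity rules are commonly left to an SAP, and none is shown. But which time point is primary is something this protocol does address, and it does so inconsistently. An SAP would have to choose between its sections.

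**Conclusion.** The point holds as an unreconciled conflict over which test is primary. It is not a demonstrated error rate. The Hypothesis section gives one time point, the Outcome measures section gives none, and the Data analysis section gives several at an unadjusted 0.05.

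If any visit may be claimed, the false-positive chance is about 8% to 14%, or 1.7 to 2.9 times the nominal 5%. This rests on an assumed between-visit correlation from 0.9 down to 0. If the 9-month test alone decides, in one form, it is 5%. The protocol does not say clearly enough which of these applies, and its sample size is consistent only with the second.

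The open choice between mean and proportion is a real gap that could raise the error further, but only if both were tested as primary.

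**What to change.** State in the Outcome measures and Data analysis sections that the primary analysis is the between-arm comparison of adherence at 9 months, in one named form, tested once at two-sided 0.05. State that months 3 and 6, and the other form, are secondary.

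Nine months follows from the Hypothesis section. The choice between mean and proportion is for the investigators, and the Sample size section should then rest on the form chosen. For that choice: 220 × 0.8 = 176, or 88 per arm after the planned loss. That is above the 86 needed for the mean and 3 short of the 91 given for the proportion. Without the continuity correction, 88 per arm gives 83% power for 60% against 80%. If the proportion is chosen, the cut-off for being adherent must be stated.

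The cost is wording in three sections, with no change to data collection or to the number recruited. It should be done before outcome data are seen, because a later choice of visit or form would not be credible. If the investigators do want all three visits to be primary, they need a prespecified multiplicity procedure and a larger trial (step 4 of the working). A single model using all visits is optional: it does not resolve which comparison decides and is not needed here.

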**Trial data collection**

Trial data will be collected at 4 time points (at baseline, 3, 6 and 9 months). Data will be collected at face-to-face during home visits, phone calls or via skype interviews (mainly for rural participants). To encourage participant retention and completeness of data, participants will receive a honourarium of AUD$30 in total at completion of the study.

At the point of recruitment into the trial, baseline data will be collected after written informed has been obtained by a member of the research team. The following information will be collected:

Sociodemographic information: Date of birth, gender, ethnicity, height, weight, education status, marital status, employment status, smoking status and health literacy

Medical history: comorbidities, NYHA class, standardised mini-mental state exam score, depression score, all prescribed and non-prescribed medication history

Laboratory test results: full blood counts, full electrolytes (sodium, potassium, urea, creatinine +/- magnesium), Hb, iron studies, NT pro BNP, liver function tests.

Functional assessment: QoL questionnaire using the Short Form 36 Health Survey version 2 (SF-36v2) (Ware JE; RAND Corporation 2015), Depression Anxiety and Stress Scales (DASS), Self-Care of Heart Failure Index (SCHFI) (Riegel et al., 2009), EQ-5D-5L questionnaire (Herdman et al., 2011) and drug adherence questionnaire, healthcare utilization (linkage data from Australian Pharmaceutical benefits Scheme and Medicare Benefits Schedule).

At the 3, 6 and 9 month follow ups, a member of the research team will record details of any changes to the participants’ medication or implantable cardiac devices, details of any hospitalisations or healthcare resource utilization since the last follow up. At each follow up interview, participants in the control arm will be asked whether they have used any drug administration aids or medication reminder app or other forms of electronic reminder systems for daily administration of medications. At the end of the study, intervention arm participants will complete a satisfaction survey to assess the acceptability, utility and engagement with the NPS MedicineWise application. Also, data about prescription refill rates and healthcare utilization will be gathered for all participants through data linkage with the Australian Pharmaceutical benefits Scheme and Medicare Benefits Schedule.

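### The only adjustment model and effect measure that the protocol names, logistic regression and odds ratios, do not fit outcomes analysed as continuous scores, and covariates are not fixed in advance

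*Protocol*

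**What the plan says.** The protocol's Data analysis section fixes four things.

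- The basic tests: "Continuous variables will be analysed using independent t-tests and discreet variables will be analyses using chi-squared tests".
- The adjustment: "Identification of any confounding baseline variables will be corrected by logistic regression analysis". No covariate is named, no rule for identifying one is given, and no linear model appears.
- The effect measure: "All between group outcome results that are significant will be reported with odds ratios and 95 % confidence intervals".
- A general allowance: "Where appropriate, other statistical tests will be employed depending on the nature of the data".

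The primary outcome (Outcome measures) is a scale: "Medication adherence will be measured by self-reported medication adherence tool Self-Efficacy for Appropriate Medication Use Scale (SEAMS"). The section does not say whether it is analysed as a score or as adherent versus not adherent. The Hypothesis section places the primary comparison at 9 months.

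The Sample size section works from two measures: a difference in mean adherence (15, SD 35, giving 86 per group) and a proportion adherent (60% versus 80%, giving 182 in total). The second sets the size of the trial.

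On baseline data, Trial data collection says "Trial data will be collected at 4 time points (at baseline, 3, 6 and 9 months"), and its baseline list includes "EQ-5D-5L questionnaire (Herdman et al., 2011) and drug adherence questionnaire". SEAMS is not named in that list, and the 6-minute walk test is absent from it.

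**The concern.** Two faults sit in the same few lines.

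**Model and outcome do not match.** SEAMS, EQ-5D-5L, DASS, the self-care index and walk distance all produce scores or measurements. If they are compared by t-test, the result is a difference in means. Logistic regression models the log odds of a binary outcome, so it cannot return an adjusted version of that difference, and an odds ratio cannot report it. The analyst must either depart from the protocol or dichotomise, and for SEAMS the protocol gives no cut-off.

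**Covariates are found, not fixed.** Under random allocation, baseline differences between arms arise by chance. Adjusting for whatever is later judged to be confounding means that the adjusted analysis is chosen after the data are seen. The protocol sets no rule for that choice, so more than one adjusted result could be presented as the planned one.

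A third, smaller matter is lost precision. An adherence questionnaire is taken at baseline, but the named analysis of the score makes no use of it.

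**Working it through.** **1. What each named method can deliver**

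| Form of the outcome | Named test | Named adjustment | Named effect measure | Consistent? |
|---|---|---|---|---|
| Score (mean difference) | t-test | logistic regression | odds ratio | No |
| Adherent yes/no | chi-squared | logistic regression | odds ratio | Yes, once a cut-off is defined |

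The plan is coherent only in the second row, and there the cut-off is missing.

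**2. Reproducing the protocol's figure for means**

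Inputs from Sample size: difference 15, SD 35, two-sided 0.05, power 80%.

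n per group = 2(1.960 + 0.842)² × 35² / 15² = 85.5, rounded up to **86**, as stated. This is the size for an unadjusted comparison, so the planned t-test and the planned size agree.

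**3. What baseline adjustment would add**

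Completers: 110 per arm less 20% = 88 per arm. The protocol gives no baseline-to-follow-up correlation r, so 0.3 to 0.7 is an assumed range. It also does not say that the 15 and 35 are on the SEAMS scale; carrying them over is a second assumption.

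With ANCOVA the residual SD is 35√(1 − r²), the standard error of the difference is that SD × √(2/88), and the noncentrality is 15 divided by the standard error. Power is from the noncentral t distribution. The required n is 85.5 × (1 − r²), rounded up.

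| r | Residual SD | SE | 15/SE | Power at 88 per arm | n per arm for 80% |
|---|---|---|---|---|---|
| unadjusted | 35.0 | 5.28 | 2.84 | 81% | 86 |
| 0.3 | 33.4 | 5.03 | 2.98 | 84% | 78 |
| 0.5 | 30.3 | 4.57 | 3.28 | 90% | 65 |
| 0.7 | 25.0 | 3.77 | 3.98 | 98% | 44 |

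A simulation of 20,000 trials per setting gave 84%, 90% and 98% for ANCOVA and about 81% (80% to 81%) for the t-test.

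**4. What dichotomising the score would cost**

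This assumes a normal score and the same standardised difference, 15/35 = 0.43.

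- Cut midway between the arm means: 41.5% versus 58.5% adherent, power at 88 per arm about 62%.
- Cut so that 60% of controls are adherent: 60% versus 75.2%, power about 58%.

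Both compare with 81% for the t-test on the uncut score. They are illustrations, because the protocol defines no cut.

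**The case against.** **The outcome may be meant as binary.** The proportion-adherent measure sets the adopted 91 per arm, and with it chi-squared, logistic regression and odds ratios belong together. This stands: the mismatch is conditional on analysing SEAMS as a score. It does not clear the text, because no SEAMS cut-off is given, the means version is also in the plan, and the t-test sentence covers continuous variables generally.

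**The t-test is valid.** It is, under randomisation, and it matches the 86 per group. A reader might infer that omitting the baseline score biases the primary comparison or leaves it underpowered. Neither follows: planned power is met at 88 per arm, and only efficiency is lost.

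**Details belong in the analysis plan.** A covariate list and the choice between ANCOVA and a repeated-measures model can be left there. But the protocol goes further and names one adjustment model and one effect measure without limit. The allowance for other tests does not alter either.

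**False positives.** A reader might infer that the plan inflates type I error. The protocol does not support a figure, since it gives no selection rule. If adjustment were triggered by a baseline difference at p<0.05 (a rule that the protocol does not contain), simulated type I error is about 5.1%, 4.3% and 3.7% at r = 0.3, 0.5 and 0.7, so it is at or below nominal, with power of 81% to 82%. Taking the smaller of the adjusted and unadjusted p-values would give 6.5% to 8.4%, but the protocol does not plan that. What stands is that the choice is left open.

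**Conclusion.** The point holds for outcomes analysed as continuous. The Data analysis section applies logistic regression and odds ratios without distinguishing scores from binary outcomes, and it leaves covariates to be identified from the data. As written, the adjustment cannot be carried out on a SEAMS mean difference.

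The unadjusted t-test remains a valid primary comparison. Adjusting for baseline is an efficiency gain: from 81% power to 84%, 90% or 98% at 88 per arm. That range rests on assumed correlations of 0.3, 0.5 and 0.7, on the 15-point difference and SD of 35 applying to SEAMS, and on the baseline questionnaire being SEAMS. The mismatch between model and outcome depends on none of these.

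It would go too far to say that the model is wrong for the primary outcome in every form, because logistic regression would suit the proportion-adherent version once a cut-off is set. The point should be corrected, but it does not invalidate the trial.

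**What to change.** In Data analysis:

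- **Continuous outcomes.** State that the 9-month score is compared by a linear model (ANCOVA, or a repeated-measures model using 3, 6 and 9 months), adjusted for the baseline value of the same score where it is collected, with any further covariates named in advance and used whatever the observed balance. Report the adjusted mean difference with its 95% confidence interval whether or not it is significant.
- **Binary outcomes.** Keep logistic regression and odds ratios here only, also with covariates fixed in advance. If SEAMS is to be analysed as adherent versus not adherent, state the cut-off.
- **Delete** the search for confounding baseline variables.

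In Trial data collection, confirm that the baseline adherence questionnaire is SEAMS. The 6-minute walk test is not in the baseline list, so as the protocol stands it cannot be adjusted for its own baseline; it would be analysed without that term unless a baseline test is in fact done.

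The cost is a small change in wording and analysis. No larger sample is needed, and no new data are needed for the primary score if the baseline questionnaire is SEAMS.

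### The protocol promises effect estimates and confidence intervals only for significant results, and names the odds ratio for all of them although continuous outcomes are to be t-tested

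*Protocol*

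**What the plan says.** Four statements in the protocol's Data analysis section bear on this point.

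- Tests: "Continuous variables will be analysed using independent t-tests and discreet variables will be analyses using chi-squared tests".
- Adjustment: "Identification of any confounding baseline variables will be corrected by logistic regression analysis".
- Reporting: "All between group outcome results that are significant will be reported with odds ratios and 95 % confidence intervals".
- Threshold: "Statistical significance is set at α 0.05".

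The Outcome measures section defines the primary outcome: "Medication adherence will be measured by self-reported medication adherence tool Self-Efficacy for Appropriate Medication Use Scale (SEAMS"). It gives no score above which a participant counts as adherent, and neither does any other section. The secondary outcomes include EQ-5D-5L, the 6-minute walk test, DASS and the self-care of HF index.

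The Sample size section sizes the trial in two ways: on a difference in mean adherence, and on the proportion of adherent participants (60% against 80%). The economic part of Data analysis separately commits to incremental cost-effectiveness ratios with confidence intervals, with no condition on significance.

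**The concern.** There are two faults in one sentence.

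**Reporting depends on the p-value.** An estimate and interval are promised for results that pass 0.05, and nothing is promised for the rest. Without an interval, a reader of a non-significant result cannot tell evidence of little or no effect from plain imprecision. The estimates that do appear have been selected for being large, so on average they overstate the effect.

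**The effect measure does not fit the test.** The odds ratio is named for all the between-group results that the sentence covers. A t-test compares means and has no odds ratio. For the continuous outcomes the stated measure cannot be obtained from the stated analysis. An analyst would have to dichotomise the scale at a cut-point the protocol does not give, or depart from the protocol.

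Both faults lie in what the protocol states, not in detail that could be left to a statistical analysis plan. A plan that followed this sentence would inherit the rule, and one that did not would contradict the protocol.

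**Working it through.** **1. The protocol's own figures reproduce.** The Sample size section gives "The first measure takes into account an absolute increase in mean adherence of 15" per cent, "at two tailed 0.05 significance level with a power of 80 % and standard deviation of 35", and 86 per group.

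- Means: n = 2 × (1.96 + 0.8416)² × 35² / 15² = 85.5, rounded up to 86 per group. This matches.
- Proportions, 60% against 80%: 82 per arm without continuity correction and 91 with it, so 182 in total. This matches with the correction.

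**2. Effect measure against test.**

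| Outcome | Test under Data analysis | What that test estimates | Measure named |
|---|---|---|---|
| EQ-5D-5L, DASS, self-care index, 6-minute walk | independent t-test | mean difference | odds ratio |
| SEAMS as a score | independent t-test | mean difference | odds ratio |
| Adherent yes/no (60% against 80%) | chi-squared | difference in proportions or odds ratio | odds ratio |

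The measure fits the last row only. There the design rates give (0.80/0.20) / (0.60/0.40) = 4 / 1.5 = 2.67. That version of the primary outcome has no cut-off in the protocol.

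**3. Which results would carry no promised interval.** The inputs are SD 35 (Sample size) and 88 completers per arm, which is 110 × (1 − 0.20), with 110 and the 20% loss from the same section. The SD belongs to percentage adherence, so this is an illustration and not a statement about SEAMS points.

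- Standard error = 35 × √(2/88) = 5.28.
- Critical difference = 1.974 × 5.28 = 10.4 points (t, 174 degrees of freedom). With 1.96 in place of 1.974 it is 10.3.

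Any observed difference smaller than about 10.4 falls outside the promise.

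**4. Average of the estimates that are promised.** Treat the estimate as normal with mean δ and SE 5.28, and let c = 10.4. Put a = (c − δ)/SE and b = (−c − δ)/SE. The probability of significance is P = [1 − Φ(a)] + Φ(b). The mean absolute estimate given significance is {δ[1 − Φ(a)] − δΦ(b) + SE[φ(a) + φ(b)]} / P.

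| True difference δ | Status | Probability of significance | Mean significant estimate | Ratio to truth |
|---|---|---|---|---|
| 15 | protocol's design value | 0.81 | 16.8 | 1.12 |
| 10 | assumed | 0.47 | 14.5 | 1.45 |
| 5 | assumed | 0.15 | 13.1 (absolute value) | 2.6 |

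For δ = 15: a = −0.87, 1 − Φ(a) = 0.808, φ(a) = 0.273, and the lower tail is negligible. The mean is 15 + 5.28 × 0.273 / 0.808 = 16.8. Simulation using 1.96 gave 16.8, 14.4 and 13.1, in agreement.

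The complement of the third column is the chance that the comparison is left without a promised interval: about 19% at the design difference, 53% at 10 points and 85% at 5.

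**The case against.** **The sentence does not say that other results will go without estimates.** This is true. A reader might infer that the protocol forbids intervals for non-significant results, and the text does not go that far. It promises them for significant results and is silent on the rest. The restriction to significant results would still serve no purpose if every result were to be treated alike. The economic part of the same section shows that an unconditional commitment could be written, but it covers only the cost-effectiveness ratios.

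**The odds ratios may be the output of the logistic regression in the preceding sentence, and the section allows other tests where appropriate.** The first reading is possible, but the sentence speaks of all between-group outcome results, and logistic regression needs a categorical outcome in any case. The allowance concerns the choice of test, not the effect measure.

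**An odds ratio does exist for the primary outcome if it is analysed as a proportion.** A reader might conclude that the primary comparison has no valid effect measure at all. The documents do not support that, because the calculation that sets the sample size is the 60% against 80% comparison. The claim about the primary outcome is therefore conditional on SEAMS being analysed as a score. The absence of any cut-off implies that it would be.

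**The inflation looks large only for small true effects.** This stands. At the design difference of 15 it is 1.12 times. The larger ratios rest on assumed differences of 10 and 5.

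A reader might also count nine secondary outcomes at three visits as 27 tests and expect 1.35 false positives to be the results that get reported. That count is wrong: the satisfaction survey is completed by the intervention arm only, at the end of the study. At most 8 × 3 = 24 secondary tests remain (24 × 0.05 = 1.2), and multiplicity is in any case a separate matter from this sentence.

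**Conclusion.** The point holds. The protocol makes the promised estimate and 95% CI depend on significance for every clinical outcome, and the one effect measure it names does not fit the test it prescribes for continuous outcomes. The second fault is certain for the continuous secondary outcomes. For the primary it depends on SEAMS being analysed as a score.

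The consequence is modest at the effect the trial was designed to find and grows as the true effect shrinks. The point figures assume 88 completers per arm and an SD stated for percentage adherence. The ratios depend only on the true difference relative to its standard error, so they carry over to any scale with the same power.

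The fault affects what is published and how it can be read. It does not affect the validity of the tests, the design or the sample size. It should be corrected before analysis.

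**What to change.** Replace the reporting sentence in Data analysis with:

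> Every prespecified primary and secondary between-group comparison will be reported with its effect estimate and 95% CI regardless of its p-value, on the scale of its analysis: mean difference for continuous outcomes, odds ratio (or risk difference) for binary outcomes.

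The cost is one sentence in the protocol and a few more rows in the results tables. No participant, visit, measurement or test is added.
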